## Abstract

**Background:**

In the past two decades, the massive scale-up of long-lasting insecticidal nets (LLINs) and indoor residual spraying (IRS) has led to significant reductions in malaria mortality and morbidity. Nonetheless, the malaria burden remains high, and a dozen countries in Africa show a trend of increasing malaria incidence over the past several years. This underscores the need to improve the effectiveness of interventions by optimizing first-line intervention tools and integrating newly approved products into control programs. Because transmission settings and vector ecologies vary from place to place, malaria interventions should be adapted and readapted over time in response to evolving malaria risks. An adaptive approach based on local malaria epidemiology and vector ecology may lead to significant reductions in malaria incidence and transmission risk.

**Methods/design:**

This study will use a longitudinal block-cluster sequential multiple assignment randomized trial (SMART) design with longitudinal outcome measures for a period of 3 years to develop an adaptive intervention for malaria control in western Kenya, the first adaptive trial for malaria control. The primary outcome is clinical malaria incidence rate. This will be a two-stage trial with 36 clusters for the initial trial. At the beginning of stage 1, all clusters will be randomized with equal probability to either LLIN, piperonyl butoxide-treated LLIN (PBO Nets), or LLIN + IRS by block randomization based on their respective malaria risks. Intervention effectiveness will be evaluated with 12 months of follow-up monitoring. At the end of the 12-month follow-up, clusters will be assessed for “response” versus “non-response” to PBO Nets or LLIN + IRS based on the change in clinical malaria incidence rate and a pre-defined threshold value of cost-effectiveness set by the Ministry of Health. At the beginning of stage 2, if an intervention was effective in stage 1, then the intervention will be continued. Non-responders to stage 1 PBO Net treatment will be randomized equally to either PBO Nets + LSM (larval source management) or an intervention determined by an enhanced reinforcement learning method. Similarly, non-responders to stage 1 LLIN + IRS treatment will be randomized equally to either LLIN + IRS + LSM or PBO Nets + IRS. There will be an 18-month evaluation follow-up period for stage 2 interventions. We will monitor indoor and outdoor vector abundance using light traps. Clinical malaria will be monitored through active case surveillance. Cost-effectiveness of the interventions will be assessed using *Q*-learning.

**Discussion:**

This novel adaptive intervention strategy will optimize existing malaria vector control tools while allowing for the integration of new control products and approaches in the future to find the most cost-effective malaria control strategies in different settings. Given the urgent global need for optimization of malaria control tools, this study can have far-reaching implications for malaria control and elimination.

**Trial registration:**

US National Institutes of Health, study ID NCT04182126. Registered on 26 November 2019.

## Background

Tremendous progress has been made in malaria control in Africa over the past two decades. This is the result of effective vector interventions, particularly the massive scale-up of long-lasting insecticide-treated nets (LLINs) and indoor residual spraying (IRS), as well as improvements in diagnostic testing and expanded availability of artemisinin-combination therapy (ACT). Nonetheless, current first-line interventions are not sufficient to eliminate malaria in many countries, and a dozen countries in Africa show a trend of increasing malaria incidence over the past several years [1]. Vector control is an important component of national malaria control strategies in Africa, and the core vector control methods are LLINs, IRS, and larval source management (LSM) [2, 3]. However, the massive scale-up of LLINs and IRS has led to major changes in vector biology, which pose significant new challenges to malaria control and elimination.

Insecticide resistance is rising rapidly, and pyrethroid resistance has been documented in malaria vectors in most countries throughout the Afrotropical region [4]. All major malaria vectors in Africa, including *Anopheles gambiae*, *Anopheles funestus*, and *Anopheles arabiensis*, are highly resistant to pyrethroids [5–7] and to multiple classes of insecticides [8, 9], resulting in limited viable insecticides for IRS. In addition to the significant problem posed by insecticide resistance, outdoor transmission is becoming increasingly common. Recent studies document a behavioral shift in malaria vectors, from midnight biting to biting in the early evening and morning when people are outdoors and not protected by IRS or LLINs [10–12]. The first-line control measures (LLINs and IRS) only protect residents sleeping under nets or resting indoors. Outdoor malaria transmission has become a very important challenge to malaria control. More importantly, malaria risk is dynamic and spatially heterogeneous. Malaria risk fluctuates over time and is associated with the success of control programs [13–16]. It may vary among villages due to micro-geographic variations in vector ecology [17, 18], residents’ health-seeking behaviors [19], socioeconomic factors, and other reasons [20–22]. The effectiveness of a control method in one setting is not always guaranteed elsewhere. Control methods need to be adapted to local malaria risks and vector ecology [23].

The problem of how to optimize intervention strategies to maintain the current progress toward eventual malaria elimination has become an important one. In Africa, the core malaria vector control tools are LLINs, IRS, and LSM [2, 3]. However, there is little knowledge regarding how these interventions should be combined in order to optimize their impact on the malaria burden. IRS is an expensive method of malaria control [24], and LSM is labor intensive and requires strong and sustained community participation [25]. Under what epidemiological settings will IRS exhibit the highest impact, and at what frequency should it be applied? Where should LSM be implemented to further reduce malaria transmission and morbidity? In addition, it is imperative that newly approved control tools, e.g., next-generation nets, new larvicide formulations, and new classes of IRS insecticides, be incorporated into control programs. How, when, and where should these tools be integrated into malaria control programs that rely on current first-line intervention tools?

In recent field tests, some new intervention tools have shown promise against insecticide-resistant malaria vectors and outdoor transmission. These include long-lasting piperonyl butoxide-treated nets (PBO Nets), long-lasting larvicides, and non-pyrethroid insecticides for IRS. All currently deployed LLINs worldwide are pyrethroid-based, despite high insecticide resistance in malaria mosquito vectors [26]. Recently, next-generation LLINs combining the synergist PBO with pyrethroids were recommended by the WHO to combat pyrethroid resistance [27]. PBO enhances the effects of pyrethroids on mosquito vectors, thus reducing vector resistance. Field studies in Africa found that compared to regular LLINs, PBO Nets significantly reduced malaria transmission in areas of high pyrethroid resistance [28–33]. Larval source management has been recommended as a public health intervention tool in specific locations where habitats are relatively few and readily identified [2, 3]. New US Environmental Protection Agency (EPA)-approved long-lasting microbial larvicides are now available. These larvicides are released slowly, thereby increasing their effective duration to 3–5 months and reducing operational costs [34]. On the other hand, the dynamic and cryptic nature of larval habitats may allow for only a portion of habitats to be identified and treated. Would new long-lasting larvicides, potentially more cost-effective than larvicides used in the past, provide added benefit to malaria control? Apart from pyrethroid insecticide IRS, new classes of insecticides, e.g., Actellic, an organophosphate, have recently been introduced for IRS in Africa [2, 3]. Field tests in several African countries found that these new IRS treatments significantly reduced malaria transmission in areas with moderate to high vector resistance to pyrethroids [15, 28, 35]. These non-pyrethroid insecticides are expected to be more expensive but also more effective against pyrethroid-resistant vectors. Given the prevalent outdoor resting behavior of mosquito vectors, will the non-pyrethroid insecticides provide added benefit and be cost-effective for malaria control?

The commonly used trial design in malaria control is randomized controlled trials (RCTs) or cluster-randomized trial (CRT) [28, 34, 36–39], which is considered the gold standard for assessing the relative efficacy of competing treatment options in evidence-based disease management [40]. Future malaria control strategies will likely involve in combination of different types of interventions, such as LLINs plus LSM or other interventions to control insecticide-resistant and outdoor vectors [28, 34, 36–39, 41–45]. Due to the potential large sample size requirement, a complete factorial design of RCT or CRT is not a practical way to find the robust combination among the many available interventions. A multi-stage adaptive intervention may be an appropriate and cost-saving approach. An adaptive design is loosely defined as a trial design that allows modifications to the trial procedure after its initiation without undermining its validity and integrity [46–49]. One way to inform the development of adaptive intervention is to randomly sequentially (during different stages of the intervention) assign different interventions to different arms or different subjects to different interventions, i.e., the sequential multiple assignment randomized trial (SMART) [46]. Unlike in conventional RCT/CRT, which treats all interventions/subjects equally and fixed throughout a trial, in adaptive interventions, decisions must be made concerning if and when an intervention needs to be continued or replaced or terminated, and accordingly, which intervention should follow. In this context, future subjects are randomized with bias toward the best-performing interventions. Adaptive design has frequently been used in clinical studies in areas such as psychology, mental health, and cancer treatment [46–49], but it has not been used in studies on vector and vector-borne infectious disease control.

The aim of this trial is to design optimal adaptive combinations of vector control interventions to maximize reductions in malaria burden based on local malaria transmission risks, vector ecology, and the available mix of interventions approved by the Ministry of Health (MoH) of Kenya. The hypothesis is that an adaptive approach based on local malaria risk and changing vector ecology will lead to significant reductions in malaria incidence and transmission risk. This paper describes a protocol for finding the optimal combination of interventions using a cluster-randomized sequential multiple assignment randomized trial (SMART) design in Kenya.

## Methods/design

### Hypothesis, interventions, and endpoint outcomes

#### Hypothesis

An adaptive approach based on local malaria risk and changing vector ecology will lead to significant reductions in malaria incidence and transmission risk.

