### Trial design and outcome measures

#### Initial cluster randomization

The SMART trial design includes two intervention stages (Fig. 2 and Table 1). Based on pre-intervention malaria risk analysis, study clusters will be stratified into three blocks with different risk levels as described above. In each block, clusters will be randomly assigned with equal probability to one of the three interventions in stage 1, i.e., LLIN, PBO LLIN, and LLIN + IRS (Fig. 2). Cluster randomization will be done using computer-generated random numbers. Ideally, each block will include 12 clusters and each of the three interventions will be assigned to four clusters in each block (Fig. 1).

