#### Sample size justification

The primary aim of this study is to determine which initial intervention, PBO LLIN or LLIN + IRS, is more effective in reducing malaria incidence after 36 months. The second aim is to estimate the mean outcomes of the 4 embedded adaptive interventions from months 16 to 36 and to identify the most effective intervention. Sample size calculation is based on the primary aim, using the primary outcome (clinical malaria incidence) and between-group comparison of the average clinical malaria incidence at month 36. The proposed sample size (*n* = 36 clusters) will detect a 10% reduction in clinical malaria incidence with 89.2% power using the current incidence rate in the study sites (302 clinic cases per 1000 person-years) and a 2-tailed *α* = 0.05 with a human population size of 500 per cluster (Table 3). If malaria incidence is 30% lower than the current value, the design will still detect a 20% incidence reduction with 97% power (Table 3). This calculation assumes a 1:1 response/non-response ratio, a fixed cluster size of 500 participants, and an intra-cluster correlation coefficient of 0.05 [89]. This sample size is likely powered to detect smaller changes in incidence reduction, as previous studies in Kenya and Ghana indicated intra-cluster correlation coefficients of < 0.02 [90].

**Table 3 Tab3:** Power calculation (%) for proposed cluster-randomized SMART trial. Shown are degrees of power to detect four levels of incidence reduction under three incidence scenarios

Annual incidence rate (cases/1000 population)	Reduction in malaria incidence			
	40%	30%	20%	10%
Observed in the site: 302	> 99.9	> 99.9	> 99.9	89.2
30% lower value: 211	> 99.9	99.8	97.0	59.0
30% higher value: 393	> 99.9	> 99.9	> 99.9	97.0

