### Data analysis

Differences in clinical malaria incidence and vector abundance between the treatment and control groups will be analyzed using Poisson multivariate regression models with intervention, malaria risk, cluster, and calendar time as covariates, using a generalized estimating equation (GEE) approach with population at each cluster as an offset [96]. GEE is necessary because incidence will be modeled monthly as a longitudinal measure using grouped data. Intervention will be a time-varying covariate, since the treatment in a cluster may be adapted and readapted depending on the response to the previous treatment. The odds ratio and 95% confidence interval for clinical malaria rates between the treatment groups and the control group will be calculated. For the second aim analysis (estimation of outcomes for the 4 embedded adaptive interventions), weighted and replicated generalized estimating equations will be used to estimate the mean clinical malaria incidence rates among the 4 embedded adaptive interventions and to compare the slopes at each stage for each adaptive intervention. Here, weighting is necessary to account for the potential over- or underrepresentation of some groups (e.g., non-responders would have a 1/4 chance of following their assigned treatment sequence, whereas responders would have a 1/2 chance of following their assigned treatment sequence) [97, 98].

We will identify a final intervention strategy after all cost and effectiveness data are collected. The aim of this strategy will be to recommend an optimal intervention method given the local conditions at each site. For this purpose, we will adopt the *Q*-learning framework from the previous section on enhanced machine learning methods [99]. We will train a neural network to predict each method’s utility, accounting for both effectiveness (reduction in malaria incidence rate) and cost based on the conditions at each site, such as malaria risk and socioeconomic, entomological, and genetic features. All data collected throughout this research will be used to train the final model. To reduce model complexity, we will consider clustering sites into a small number of classes and then training a model to predict the efficacy of each method conditioned on each class. Once the *Q*-function is learned, we will identify the optimal intervention by choosing the intervention method that maximizes the learned *Q*-function.

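### The hypothesis that an adaptive approach reduces malaria has no matching contrast: no embedded strategy is compared with the concurrent LLIN control

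*Protocol article*

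**What the plan says.** The Hypothesis section states: "An adaptive approach based on local malaria risk and changing vector ecology will lead to significant reductions in malaria incidence and transmission risk". It names no comparator.

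Sample size justification fixes two aims. The primary aim is to "determine which initial intervention, PBO LLIN or LLIN + IRS, is more effective in reducing malaria incidence after 36 months". The second is to "estimate the mean outcomes of the 4 embedded adaptive interventions from months 16 to 36 and to identify the most effective intervention".

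Data analysis describes two models.

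- **Treatment versus control:** "Differences in clinical malaria incidence and vector abundance between the treatment and control groups will be analyzed using Poisson multivariate regression models". This is fitted by GEE with intervention as a time-varying covariate, and a ratio with 95% confidence interval against control is reported.
- **Strategies:** "weighted and replicated generalized estimating equations will be used to estimate the mean clinical malaria incidence rates among the 4 embedded adaptive interventions". Slopes by stage are also compared for each strategy. The weighting is explained by saying that "non-responders would have a 1/4 chance of following their assigned treatment sequence, whereas responders would have a 1/2 chance".

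Under Initial cluster randomization, "clusters will be randomly assigned with equal probability to one of the three interventions in stage 1", ideally four clusters per intervention in each of three blocks. Stage 2 intervention and Table 2 list four embedded strategies, all starting with PBO LLIN or LLIN + IRS. Cost-effectiveness analysis compares the two intervention groups with control and, separately, the four strategies with one another.

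**The concern.** A claim of reduction needs something to be reduced against. The Stage 1 intervention section explains why a concurrent LLIN group is needed when judging response: incidence shifts between seasons and years, and LLIN is the routine government intervention. The same reasoning applies to the hypothesis, yet each aim or analysis that concerns the adaptive strategies leaves LLIN out.

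At stake is whether the trial can answer its own headline question. It may identify the best of four strategies and still be unable to say, from a randomised comparison, whether that strategy does better than current practice. An analysis plan written to these aims would inherit the gap, so this is more than detail deferred to a later document.

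**Working it through.** **1. Each planned comparison set against the hypothesis**

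| Place | What is compared | Strategy v LLIN? |
|---|---|---|
| Primary aim | PBO LLIN start v LLIN + IRS start | No, LLIN absent |
| Second aim | Four strategies, best one chosen | No, LLIN absent |
| Weighted and replicated GEE | Four strategies with one another | No |
| Cost-effectiveness | Intervention groups v control; four strategies with one another | No, the two sets are kept apart |
| Treatment-control GEE | Current intervention v control | Not for a strategy (step 2) |

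**2. Why the treatment-control GEE does not fill the gap**

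By the stage 1 and stage 2 rules, clusters still on PBO LLIN alone in stage 2 are the responders, and every PBO LLIN + LSM cluster is a non-responder. The same holds for LLIN + IRS and its two modified versions. A stage 2 coefficient for the current intervention therefore compares LLIN clusters, which are not selected on response, with clusters selected on a post-randomisation outcome. This tends to flatter continued treatment and penalise added treatment. The risk and cluster covariates cannot be relied on to undo selection on stage 1 response. A strategy such as PBO LLIN with LSM added on non-response is a mixture of both groups, and no single coefficient estimates it.

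**3. The weights**

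- Three-arm probabilities: responders 1/3; non-responders 1/3 × 1/2 = 1/6. Inverse weights 3 and 6.
- Conditional on the 24 clusters in the two active arms: responders (1/3)/(2/3) = 1/2; non-responders 1/2 × 1/2 = 1/4. Inverse weights 2 and 4, which reproduces the protocol's figures.
- 3:6 equals 2:4. The common factor of 1.5 cancels, so estimates and robust standard errors for the four strategies do not change. A weighted, replicated Poisson GEE on simulated data gave the same four rates (0.25022, 0.23867, 0.24744, 0.24767) and the same standard errors on either scale.

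**4. Precision of the missing contrast**

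Inputs from the protocol: 12 clusters per arm, 1:1 response, ICC 0.05 (with < 0.02 cited from previous studies), 302 cases per 1000 person-years. Assumption: the rate is treated as a one-year binary risk to convert ICC to a between-cluster CV.

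- Each strategy has 6 responders (weight 1) and 6/2 = 3 non-responders (weight 2).
- Effective clusters = (6×1 + 3×2)² / (6×1² + 3×2²) = 144/18 = 8.
- CV = sqrt(0.05 × 0.698/0.302) = 0.34.
- SE of the log rate ratio = 0.34 × sqrt(1/8 + 1/12) = 0.155.
- Reduction detectable with 80% power = 1 − exp(−2.80 × 0.155) = 35%.

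The response ratio matters. If all clusters respond, a strategy has 12 effective clusters; if none do, it has 6. The same formulas give:

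| Contrast | SE, ICC 0.05 | 80% power at | SE, ICC 0.02 (CV 0.215) | 80% power at |
|---|---|---|---|---|
| Strategy v LLIN, 8 v 12 | 0.155 | 35% | 0.098 | 24% |
| Strategy v LLIN, 6 v 12 | 0.170 | 38% | 0.108 | 26% |
| Starting arm v LLIN, 12 v 12 | 0.139 | 32% | 0.088 | 22% |

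These use between-cluster variation only. A two-proportion calculation with design effect 1 + 499 × ICC is less favourable. For 8 v 12 clusters and reductions of 20%, 30% and 40%, it gives power of 25%, 51% and 77% at ICC 0.05, and 51%, 87% and 99% at ICC 0.02.

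**The case against.** The strongest reply is that comparisons with control are planned. Data analysis reports a ratio against control, and Cost-effectiveness analysis includes the control group. If the treatment groups there mean the randomised starting arms, then PBO-start v LLIN tests strategies 1 and 2 pooled, and IRS-start v LLIN tests 3 and 4 pooled. A reader might infer that the plan has no comparison with control at all; the documents do not support that. The reply still falls short, because the text makes intervention time-varying and never states the pooled reading.

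A second reply is that LLIN as comparator is an inference. This is true: the hypothesis names none, and the central objective is to design optimal combinations, which the second aim serves. But a hypothesis of reduction needs a reference, and the protocol's own argument for concurrent LLIN clusters points to one.

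A reader might also infer that 1/2 and 1/4 are wrong because the first randomisation has three arms. They are exact for the two active arms, and the planned estimates are unaffected. Scale would matter only if LLIN were added to a model with shared covariates at a weight inconsistent with the others, which nobody has planned.

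Finally, the new contrasts are imprecise. That stands, and is a reason to state their precision in advance.

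**Conclusion.** The point holds as a mismatch between the hypothesis and the stated comparisons: no embedded strategy is contrasted with LLIN, and the one model that includes control does not estimate a strategy effect in stage 2. It does not extend to an absence of any control comparison or to an error in the weights.

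The missing contrast is informative for large effects only: roughly a 35% reduction for 80% power at ICC 0.05 and 24% at ICC 0.02, somewhat more under the two-proportion calculation. These figures assume 1:1 response, 12 clusters per arm and the binary-risk conversion.

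The remedy also assumes that the LLIN clusters are followed through stage 2. The Data analysis and Cost-effectiveness sections imply it, but the readable text does not say so, and Figure 2 and Table 1 are not shown. A reader should not take it as documented.

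**What to change.** 1. Name LLIN as the comparator in the hypothesis and aims, and confirm that the LLIN clusters are followed through stage 2.
2. Add the LLIN clusters as a fifth, non-adapted regimen in the weighted and replicated GEE, with the same weight as responders and non-responders at twice that (2, 2 and 4, or equivalently 3, 3 and 6).
3. Prespecify one test of the hypothesis: either each strategy's rate ratio versus LLIN over months 16 to 36, or the starting-arm versus LLIN contrast with the randomised arm as a fixed covariate (12 v 12 clusters). State how multiplicity is handled across the chosen contrasts, and give their expected precision.
4. Label 1/2 and 1/4 as conditional on the two active arms, or give 1/3 and 1/6.
5. Describe the time-varying treatment-control model as an analysis of current intervention, not of strategies.

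The cost is wording and a few extra contrasts of limited precision. If stage 2 follow-up of the LLIN clusters is confirmed, no new data are needed, and the four-strategy comparison keeps its relative weights.
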